### Patients

Male and female patients aged ≥18 years diagnosed with end-stage renal disease who undergo continuous ambulatory peritoneal dialysis for 30 to 180 days are included. Patients diagnosed with diabetic kidney disease have a residual glomerular filtration rate of 3 to 15 ml/min [21], whereas patients with other renal diseases have a residual glomerular filtration rate of 3 to 10 ml/min.

All patients must provide written informed consent before undergoing any study-related procedures.

Patients are excluded if: they have acute renal failure; are candidates for kidney transplantation; are undergoing hemodialysis; have an exit site infection, tunnel infection or peritonitis according to Peritoneal Dialysis Standard Operating Procedure [22]; are anti-HIV positive; are allergic to any component of dialysis fluids; have a systemic infection, malignancy, liver cirrhosis, severe congestive heart failure, anemia (hemoglobin <80 g/l), malnutrition (albumin <28 g/l), refractory hypertension, high peritoneal transportation (*D*/*P*_Cr_ > 0.81); or are pregnant or lactating. Patients with poor compliance or a history of alcoholism or drug abuse are also excluded.

Patients are being recruited from 50 peritoneal dialysis centers throughout China. The study protocol was approved by the ethics committee of each center (Additional file 1) and is conducted according to the Declaration of Helsinki [23] and the Good Clinical Practices guidelines of the China Food and Drug Administration [24]. The study has been registered at www.clinicaltrials.gov, number NCT01779557.

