### Outcomes

The primary outcome measure is patient survival rates at 1, 2, 3, 4, and 5 years. The secondary outcome measures include peritoneal dialysis technique survival rates of 1, 2, 3, 4, and 5 years; estimated decline in glomerular filtration rate, nutritional status (represented as serum albumin and Subjective Global Assessment Score [25]), quality of life (described by the 36-Item Short-Form Health Survey [26]), cardiovascular events (cardiac sudden death, myocardial infarction, severe arrhythmia, carotid plaque, heart failure, cardiovascular intervention, coronary heart disease without myocardial infarction, stroke or transient ischemic attack, peripheral artery disease), increments of dialysis dosage from baseline to the end, and drop-out rates. Medical costs are also recorded.

Safety evaluations include adverse events and severe adverse events, marked changes of vital signs and laboratory test results, peritonitis (infectious or chemical), allergy to ingredients of peritoneal dialysis fluids and materials of bags and tubing, and quality of dialysis product. Evaluation of product quality includes the transparency of fluid bags, the tightness of connections, and the legibility of labels and texts on packaging.

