### Statistics

The primary analysis population is the per-protocol set, consisting of randomized patients with baseline data and data on primary outcome measures, as well as good compliance. This population includes patients who quit the study because of lack of drug effectiveness. The secondary analysis population is the full analysis set according to the intention-to-treat principle; this population includes all randomized patients who receive therapy at least once, regardless of whether they adhere to the protocol or provide a complete dataset. Patients who never receive therapy are excluded. Patients with missing data are included, with adjacent data carried forward to the missing data. The full analysis set population is consistent throughout the entire study. The safety analysis population is the safety set, which includes all patients who receive therapy at least once.

Patient survival rates are analyzed by constructing a Cox regression model that includes multiple variables, such as baseline glomerular filtration rate, severity of disease, age, and treatment group. A non-inferiority test is determined by computing the 95 % confidence interval of the hazard ratio. The same method is used to analyze technique survival rates. Decline in estimated glomerular filtration rate is analyzed by the Wilcoxon rank-sum test. Nutritional status and quality-of-life score are analyzed by analysis of covariance. Rates of cardiovascular events and patient drop-out are analyzed by the Cochran–Mantel–Haenszel *χ*^2^ test. Increments of dialysis dosage from baseline to the end of treatment are analyzed by constructing a mixed model. Medical costs are compared by *t* test or analysis of variance. Adverse events and severe adverse events are categorized according to terminology in the Medical Dictionary for Regulatory Activities. Adverse events, severe adverse events, peritonitis, and allergies are compared by the *χ*^2^ test or Fisher’s exact test. Product quality is evaluated by nonparametric tests.

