In China, the appropriate peritoneal dialysis dosage remains unclear. Western patients are often treated with 8 l/day, whereas 6 l/day is believed sufficient for incident peritoneal dialysis in Asian patients. Chinese patients differ ethnically from patients in Western countries. Although Chinese patients are similar ethnically to patients in Hong Kong and Japan, their economic status, which is important for peritoneal dialysis use, is quite different. Our previous study showed that 6 l/day was sufficient for adequate peritoneal dialysis in Chinese patients, although a 48-week follow-up showed continuous decline in *Kt*/*V* and creatinine clearance rate [20]. Further decreases in *Kt*/*V* and creatinine clearance rate would necessitate increases in peritoneal dialysis dosage. In this study, the observation period is 5 years. Thus, dosage could not be fixed at 6 or 8 l/day; rather, it would have to be changed according to clinical situations. The trial described here would therefore be a study of the effectiveness, not the efficacy, of peritoneal dialysis [42]. The dosage adjustment protocol in this study is almost the same as that in routine clinical circumstances.

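### Decline in GFR is tested without baseline adjustment although absolute decline cannot exceed baseline GFR; the test is valid but may lose precision that a rank analysis of covariance would recover

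*Protocol article*

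**What the plan says.** The Outcomes section of the protocol article lists decline in GFR among the secondary outcomes ("estimated decline in glomerular filtration rate, nutritional status" and others), without ranking them. The Statistics section names the test: "Decline in estimated glomerular filtration rate is analyzed by the Wilcoxon rank-sum test". It gives no covariate or stratum for it.

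Two other places bear on that choice:

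- **Entry ranges (Patients section).** "Patients diagnosed with diabetic kidney disease have a residual glomerular filtration rate of 3 to 15 ml/min", while "patients with other renal diseases have a residual glomerular filtration rate of 3 to 10 ml/min".
- **Methods for other outcomes (Statistics section).** The Cox model for survival "includes multiple variables, such as baseline glomerular filtration rate, severity of disease, age, and treatment group". Also, "Nutritional status and quality-of-life score are analyzed by analysis of covariance". Dose increments are analysed with a mixed model.

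On duration, the Discussion says: "In this study, the observation period is 5 years".

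**The concern.** Taken as an absolute change, decline is baseline GFR minus follow-up GFR, and follow-up GFR cannot go below zero. Each patient's largest possible decline is therefore the entry value. A patient entering at 3 ml/min can lose at most 3, and one entering at 15 can lose up to 15. Over five years, as patients approach zero, decline comes closer and closer to the baseline value itself. The rank-sum test then treats variation that was already known at entry as noise.

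The plan accepts baseline GFR as a covariate for survival but does not use it for the outcome that is arithmetically tied to it. What could be lost is power: a real difference between the fluids in preservation of residual renal function might be missed, and a null result might be read as more reassuring than it is.

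**Working it through.** **1. Is there a planned figure to reproduce?** No. The article gives no standard deviation, effect size, correlation, power or assessment time for GFR decline. The Sample size section (310 per group, 750 enrolled) concerns survival only.

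**2. Entry ranges (Patients section).** Diabetic kidney disease, and the trial overall: 15 / 3 = 5.0-fold. Other renal disease: 10 / 3 = 3.3-fold.

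**3. What adjustment can gain.** If r is the correlation between decline and baseline GFR, linear adjustment leaves a residual variance of 1 − r² times the unadjusted variance. The share removed is r²: 9 % at r = 0.3, 25 % at r = 0.5 and 49 % at r = 0.7.

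**4. What that means for power.** Assumptions: 310 per group (borrowed from the survival calculation), a difference of 0.2 SD, one-sided α = 0.025, normal data. The non-centrality of the unadjusted t test is 0.2 × √(310/2) = 2.49.

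| Analysis | Non-centrality | Power, Φ(non-centrality − 1.96) |
|---|---|---|
| Wilcoxon, efficiency 3/π | 2.49 × √0.955 = 2.43 | 68 % |
| ANCOVA, r = 0.3 | 2.49 / √0.91 = 2.61 | 74 % |
| ANCOVA, r = 0.5 | 2.49 / √0.75 = 2.87 | 82 % |
| ANCOVA, r = 0.7 | 2.49 / √0.51 = 3.49 | 94 % |

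With about 50 % five-year survival assumed in the Sample size section, fewer than 310 per group would have a five-year GFR. The table compares methods; it does not predict the trial's power.

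**5. Which r is plausible?** The article does not say, so two opposite models were simulated. Baseline was spread over the entry ranges (evenly or skewed), 40 % of patients were assumed diabetic, and follow-up GFR was floored at zero. Power comes from 600 runs per scenario (Monte Carlo error at most √(0.25/600), about 2 points).

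| Model of loss | Time | r | r² | Wilcoxon | ANCOVA | Rank ANCOVA |
|---|---|---|---|---|---|---|
| Proportional to baseline | 1 year | 0.52–0.59 | 0.27–0.35 | 58–60 % | 72–73 % | 70–74 % |
| Proportional to baseline | 5 years | 0.83–0.87 | 0.69–0.75 | 28–36 % | 72–75 % | 73–74 % |
| Absolute, unrelated to baseline | 1 year | about 0 | about 0 | 65–68 % | 69–73 % | 65–68 % |
| Absolute, unrelated to baseline | 5 years | 0.43–0.44 | about 0.19 | 18–27 % | 18–30 % | 22–32 % |

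The power figures depend on assumed effects and should be compared only along a row. Across the two models, r² runs from about 0 to 0.35 at 1 year and from about 0.19 to 0.75 at 5 years. In equivalent sample size, 1 / (1 − r²), that is up to 1 / 0.65 = 1.5 times at 1 year, and from 1 / 0.81 = 1.2 to 1 / 0.25 = 4 times at 5 years.

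**6. Sensitivity to the assumed speed of loss.** A second simulation assumed 30 % diabetic patients and even baselines. With proportional loss at a median rate of 0.2 to 0.5 per year (log-SD 0.6, measurement noise SD 0.5), r² at 5 years was 0.56 to 0.85. With absolute loss at a median of 0.5 to 2 ml/min per year, it was 0.01 to 0.54, rising as more patients reached zero. Pearson and Spearman correlations were nearly identical under proportional loss, so ranking does not remove the dependence on baseline.

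**The case against.** The strongest case for the plan is that nothing in it is invalid. Residual GFR piles up at zero, which gives skew and ties and is a sound reason for a rank test. Under 1:1 randomization the unadjusted Wilcoxon test keeps its type I error. All of that stands, and it is why the remedy should stay rank-based. A Gaussian repeated-measures model would handle the floor poorly and, with about 50 % five-year mortality assumed, would implicitly model GFR after death.

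The scale of decline is also unstated. If it is a percentage or a proportional rate, the bound argument largely falls away. That stands too, so the point is made for absolute decline.

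A reader might also infer stronger claims that the article does not support:

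- **Most of the precision is certainly lost.** This holds only if loss is roughly proportional to baseline. If absolute loss is unrelated to baseline, the gain is almost nil early on and modest at 5 years.
- **Chance imbalance in baseline GFR or diabetes biases the comparison.** It adds variance, which the test's null distribution already covers.
- **GFR decline is the only unadjusted outcome.** Medical costs, adverse events and product quality are also compared without covariates.
- **It is a key secondary outcome.** The Outcomes section sets no hierarchy.
- **GFR is carried forward after death.** Carry-forward is described for the full analysis set, which is the secondary population, and nothing says that it applies after death.
- **Baseline varies five-fold in everyone.** It does so in diabetic kidney disease and overall; in other disease the range is 3.3-fold.

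**Conclusion.** The point holds as a matter of precision in one secondary outcome. The article fixes an unadjusted test for a quantity that, on the absolute scale, is bounded by a baseline value already collected and already used as a covariate for survival.

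The variance that adjustment could remove is about 0 to 35 % at 1 year and about 19 to 75 % at 5 years. These ranges rest on assumed loss models, diabetic share and baseline distribution, none of which the article gives; other assumed speeds of loss widen the five-year range in both directions. The true figure is unknown, but the recommendation does not depend on it: where r was about 0, rank ANCOVA had the same simulated power as the Wilcoxon test (65–68 %), so adjusting costs practically nothing when there is nothing to gain. Neither the validity of the planned test nor the primary outcome is affected.

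**What to change.** Replace the unadjusted test, as the main analysis of GFR decline, with a rank analysis of covariance with baseline GFR and diabetic kidney disease as covariates. A Wilcoxon rank-sum test stratified by baseline GFR band and diabetic kidney disease, with the bands fixed in advance, is an acceptable alternative. State whether decline is absolute or relative, since the case for adjustment is strongest on the absolute scale. Keep the unadjusted Wilcoxon test as a sensitivity analysis.

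Both covariates are recorded at entry to establish eligibility. The change therefore needs analysis wording only, with no new data, visits or patients.

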### Sample size

The sample size is based on both Chinese facilities containing large numbers of patients [27–31] and the Chinese National Renal Data System [32], consisting of smaller units. We have estimated that the mean 5-year survival rate of patients using Baxter dialysis fluid is about 50 %, with a hazard ratio of 1.31. If the recruitment lasts 2 years and the observation 5 years, with *β* = 0.8, a one-sided *α* for the *t* test = 0.025, and 15 % censored data in each group, 310 patients per group will be needed. With a 20 % drop-out rate, 750 patients should be enrolled in this study.

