This study compares two types of peritoneal dialysis fluid, one packed in PVC and the other in non-PVC materials. It is known that PVC has deleterious effects on human health, owing to the added plasticizer (i.e., DEHP), although the significance of its toxicity may be exaggerated [43, 44], Moreover, an as-yet-unknown toxicity may manifest during long-term usage. The toxicity of the plasticizer has been confirmed [45, 46], limiting the usage in some countries of PVC materials in medical devices and food and drug utensils [47]. The Chinese National Development and Reform Committee released a catalog of industrial structural adjustments in 2011, although peritoneal dialysis fluids were excluded from the list [48]. However, use of the plasticizer remains a public and medical concern. This is not the first trial to compare PVC and non-PVC materials in peritoneal dialysis, but it is the first long-term head-to-head comparison of peritoneal dialysis fluids packed in PVC and non-PVC materials. Studies have compared the traditional PVC packed dialysis fluid *Dianeal*® and non-PVC packed peritoneal dialysis fluids, but these fluids have many differences other than their packaging, including pH and buffering agent. The two types of peritoneal dialysis fluid in this trial have the same pH, buffer, and osmotic agents, with only the packaging material differing, in that *Dianeal*® is packed in PVC and HUAREN dialysis fluid in non-PVC bags.

This study may also reveal some of the disadvantages of non-PVC material. For example, this material may be stiff and fragile, and may be prone to leakage when used for peritoneal dialysis, resulting in peritonitis. The PVC packaging has better elasticity, flexibility, and durability, making it useful as a liquid container. In a large country, such as China, peritoneal dialysis fluids travel a great distance to reach patients’ homes. Climate, temperature, and physical abrasion all challenge the packaging of dialysis fluids. Transportation of peritoneal dialysis fluids to patients in the far north of China is especially long and difficult and may have deleterious effects if the packaging is not durable. Thus, it remains unclear whether the use of non-PVC packed peritoneal dialysis fluids is feasible in China.

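### Peritonitis and cardiovascular events over 5 years are tested as patient counts without time at risk or repeat episodes: this costs power, and it biases the comparison of event rates if death or drop-out differs between arms

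*Protocol article*

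**What the plan says.** The Statistics section names the tests. For cardiovascular events it says: "Rates of cardiovascular events and patient drop-out are analyzed by the" Cochran–Mantel–Haenszel chi-square test. For safety it says: "Adverse events, severe adverse events, peritonitis, and allergies are compared by the" chi-square test or Fisher's exact test. A Cox model is kept for patient survival, and for one other outcome: "The same method is used to analyze technique survival rates".

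The Sample size section shows how uneven follow-up is expected to be. It states: "We have estimated that the mean 5-year survival rate of patients using Baxter dialysis fluid is about" 50 %, "with a hazard ratio of 1.31". It also says: "If the recruitment lasts 2 years and the observation 5 years", with 15 % censored data, a 20 % drop-out rate and 750 patients enrolled.

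The Discussion explains why peritonitis matters in this comparison. The non-PVC bag "may be prone to leakage when used for peritoneal dialysis, resulting in peritonitis". The Outcomes section lists peritonitis as a safety evaluation. It lists cardiovascular events as a secondary outcome whose components include sudden cardiac death and carotid plaque.

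**The concern.** The named tests compare how many patients in each arm had the event at least once. A patient followed for 6 months and one followed for 5 years count alike, and a patient with four peritonitis episodes counts the same as a patient with one. Stratifying a Cochran–Mantel–Haenszel test, for example by centre, does not correct for time at risk.

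Two different losses follow.

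- **Power and dilution.** This applies even if the arms are followed equally. It is largest for peritonitis, which can recur.
- **Bias as a comparison of event rates.** This applies if death or drop-out differs between arms. The arm observed for less time has fewer chances to record an event, so a real excess in that arm can be hidden and a false excess can appear in the other.

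At stake is the trial's ability to see a harm that its own Discussion raises for the new bag. The tests are written into the article, so this is not a detail left to a fuller analysis plan.

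**Working it through.** **Inputs from the article.** 750 patients at 1:1 gives 375 per arm. Control 5-year survival of about 50 % gives an exponential death hazard d = ln 2 / 5 = 0.1386 per year. Drop-out of 20 % over 5 years gives e = −ln(0.80)/5 = 0.0446 per year. The hazard ratio in the sample size paragraph is 1.31.

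**Assumed inputs.** The article gives no peritonitis or cardiovascular rate, and no drop-out by arm. There is therefore no planning figure to reproduce for these outcomes. Assumed here are peritonitis rates of 0.20 vs 0.28 episodes per patient-year, with gamma variation between patients (variance 1), and a control cardiovascular rate of 0.06 per year with a true hazard ratio of 1.31 (0.06 × 1.31 = 0.0786). Unequal drop-out, where used, is 25 % vs 15 %. Follow-up stops at 5 years.

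**Step 1: time at risk.** With total exit hazard 0.1386 + 0.0446 = 0.1833, mean follow-up is (1 − e^(−5 × 0.1833)) / 0.1833 = (1 − 0.50 × 0.80) / 0.1833 = 3.27 years, not 5.

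**Step 2: peritonitis.** Counts were simulated as gamma-Poisson with exponential death and drop-out, two-sided 5 %. Chi-square on ever/never was compared with a rate comparison (episodes per patient-year, robust variance). Several independent runs gave:

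| Scenario (HUAREN vs Baxter) | Chi-square power | Rate power | Chi-square false rejection |
|---|---|---|---|
| Equal death, 20 % drop-out in both | 50–53 % | 78–83 % | about 5 % |
| Death HR 1.31, 20 % drop-out in both | 24–25 % | 80–82 % | 10–11 % |
| Death HR 1.31, drop-out 25 % vs 15 % | 11–15 % | 80–82 % | 19–20 % |

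False rejection was obtained with 0.20 episodes per patient-year in both arms; the rate comparison stayed at about 5 %. With unequal follow-up, almost all false rejections favoured HUAREN, the arm with less time at risk.

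**Step 3: other peritonitis rates.** A second simulation used a true rate ratio of 1.3, equal mortality, one-sided 0.025 and 5 to 7 years of administrative follow-up:

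| Control rate per year | Risk ratio, ever affected | Chi-square power | Rate power |
|---|---|---|---|
| 0.2 | 1.14 | 32 % | 60 % |
| 0.4 | 1.10 | 30 % | 74 % |
| 0.6 | 1.08 | 28 % | 78 % |

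The gap does not depend on one chosen rate.

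**Step 4: cardiovascular events.** The 5-year probability of a first event, with death and drop-out as competing exits, is p = c/(c+d+e) × (1 − e^(−5(c+d+e))).

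- *Equal follow-up.* Baxter: 0.06/0.2433 × (1 − e^(−1.216)) = 0.174. HUAREN: 0.0786/0.2619 × (1 − e^(−1.309)) = 0.219. Risk ratio 1.26.
- *Death HR 1.31 in HUAREN.* d becomes 0.1816. HUAREN: 0.0786/0.3048 × (1 − e^(−1.524)) = 0.202. Risk ratio 0.202/0.174 = 1.16.
- *Also drop-out 25 % vs 15 %.* e becomes 0.0575 vs 0.0325. Baxter: 0.06/0.2311 × (1 − e^(−1.156)) = 0.178. HUAREN: 0.0786/0.3177 × (1 − e^(−1.589)) = 0.197. Risk ratio 1.11.

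For power, the second simulation took 0.1 events per year and a true ratio of 1.3. With equal mortality, chi-square reaches 44 % and log-rank 53 %. With death HR 1.31 in the HUAREN arm, they reach 17 % and 51 %.

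**Step 5: the opposite direction.** With no true difference in cardiovascular rate (0.1 to 0.4 per year) but lower HUAREN mortality (HR 1/1.31), chi-square shows a false HUAREN excess in 10–17 % of trials, against a nominal 2.5 %. Log-rank stays at about 3 %.

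**The case against.** The strongest reply is that the planned tests are legitimate. With similar death and drop-out in both arms, a chi-square test is a valid comparison of the proportion ever affected, and percentages of patients with adverse events are a conventional safety summary. These outcomes are secondary or safety outcomes. A mortality imbalance would also show in the primary Cox analysis, so the cause of the bias would not go unseen. All of this stands. It limits the weight of the point but does not recover the lost power.

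Several stronger readings are tempting, and the article does not support them.

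- *A reader might infer that the tests are biased in any case.* Bias needs unequal death or drop-out. The article gives a single 20 % drop-out figure with no split by arm, and 1.31 is a sample size input, not a forecast of excess deaths. The 25 % vs 15 % split is purely an assumption.
- *A reader might take 1.11 as the general dilution for cardiovascular events.* It needs both imbalances at once. With equal follow-up the risk ratio is 1.26, close to the true 1.31.
- *A reader might infer that every early death counts as no cardiovascular event.* Sudden cardiac death is a component, so some deaths are events.
- *A reader might extend the point to drop-out.* No harm has been shown there. A proportion is a usual summary of drop-out, and the Cox analysis of technique survival may partly cover the question.
- *A reader might assume that all event dates are on file.* The article does not say so, and carotid plaque has a date of detection, not of onset.

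The replacement has its own assumption: censoring at drop-out must be non-informative. It also targets a different quantity, the event rate or cause-specific hazard, not the proportion affected.

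**Conclusion.** The point holds for peritonitis and cardiovascular events, and most strongly for peritonitis. Under equal follow-up the planned peritonitis test gives up roughly 30 percentage points of power (about 50 % vs about 80 %). Under unequal follow-up it can also mislead on event rates: power falls to about 25 % and then 13 %, while false rejection rises to about 11 % and then 19 %. For cardiovascular events the loss is small with equal follow-up and grows only with imbalance (risk ratio 1.26, 1.16, 1.11 for a true hazard ratio of 1.31).

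The direction of the problem follows from the stated tests and the planned mortality. Its size rests on assumed event rates, exponential death and drop-out, and assumed imbalances between arms, so confidence in the exact figures is moderate. The analysis should be changed, but the primary outcome is not affected.

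**What to change.** - **Peritonitis:** compare episodes per patient-year with a negative binomial model and log follow-up time as offset.
- **Cardiovascular events:** analyse time to first event with a cause-specific Cox model, and show cumulative incidence with death as a competing event. Use the date of detection for components such as carotid plaque.
- **Adverse events:** report events per 100 patient-years beside the percentages.
- **Planned tests:** keep the Cochran–Mantel–Haenszel, chi-square and Fisher tests as supportive analyses.

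The cost is revised wording and some extra analysis, settled before the arms are compared. The new analyses need event and exit dates, so the trial team should confirm that these are recorded. They should also state the assumption of non-informative censoring at drop-out.

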**Methods/Design:**

The study participants are adults undergoing continuous ambulatory peritoneal dialysis for 30 days to 6 months. All eligible patients are randomized (1:1) to peritoneal dialysis with Baxter and HUAREN dialysis fluids (initial dose, 6 l/day), with dosages adjusted according to a unified protocol. The primary outcomes are the 1-, 2-, 3-, 4-, and 5-year overall survival rates. Secondary outcome measures include technique survival rates, reductions in estimated glomerular filtration rate, nutritional status, quality of life, cardiovascular events, medical costs and drop-out rates. Safety outcome measures include adverse events, changes in vital signs and laboratory parameters, peritonitis, allergies, and quality of products.

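### The cost comparison by t test or ANOVA makes no allowance for cost cut off at drop-out, so mean 5-year cost is biased low and unequal drop-out can create a false difference

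*Protocol article*

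**What the plan says.** The Abstract counts cost among the secondary outcomes: "cardiovascular events, medical costs and drop-out rates". The Outcomes section says only "Medical costs are also recorded", without stating whether this is a cumulative total or a cost per unit of time. The Statistics section fixes the test: "Medical costs are compared by" t test or ANOVA. For patient survival and technique survival the same section uses Cox regression, which handles censoring.

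The Sample size section puts the "mean 5-year survival rate of patients using Baxter dialysis fluid is about 50" %, "with a hazard ratio of 1.31". It assumes that "recruitment lasts 2 years and the observation 5 years", allows 15 % censored data per group, and ends: "With a 20 % drop-out rate, 750 patients should be enrolled in this study".

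Two general rules in the Statistics section bear on the point. The primary population is per-protocol; it requires primary-outcome data and good compliance but keeps patients who left for lack of effectiveness. The full analysis set, which is secondary, fills missing values by carrying adjacent data forward.

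**The concern.** A t test on recorded totals estimates the mean 5-year cost only if each patient's total is known up to death or 5 years, whichever comes first. For a patient who drops out, the total is known only up to that date. Taken at face value, someone who leaves at month 6 becomes a cheap patient. The mean in any arm with drop-out is then too low, and the arm that loses more patients looks cheaper even when a year of treatment costs the same in both.

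Differential drop-out is a live possibility. The plan itself compares drop-out between arms, and its Discussion raises the chance that the non-PVC bag leaks and leads to peritonitis. The Discussion also lists medical costs among the trial's economic aspects and addresses government policy, so a spurious saving could be cited.

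**Working it through.** The documents state no figure for the cost comparison, so there is none to reproduce. The check asks how far truncation at drop-out moves the mean.

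**Inputs from the Sample size section:** 5-year survival of 50 % on Baxter fluid, hazard ratio 1.31, drop-out 20 %, 5 years of observation.

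**Assumptions:** cost is cumulative per patient; cost per year is constant and equal in both arms; death and drop-out times are exponential and independent; each patient is followed for 5 years; 20 % is the probability of dropping out by 5 years in the absence of death. The unequal drop-out splits are illustrative.

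**Formula.** At constant cost per year, mean recorded cost is proportional to mean observed time within 5 years:

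m(h, e) = [1 − exp(−5(h + e))] / (h + e)

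Here h is the death hazard and e the drop-out hazard. The death hazard is h = ln 2 / 5 = 0.1386 per year.

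| Scenario | e | h + e | Mean observed years |
|---|---|---|---|
| No drop-out | 0 | 0.1386 | 0.50 / 0.1386 = 3.607 |
| 10 % drop-out | −ln 0.9 / 5 = 0.0211 | 0.1597 | 0.55 / 0.1597 = 3.444 |
| 20 % drop-out | −ln 0.8 / 5 = 0.0446 | 0.1833 | 0.60 / 0.1833 = 3.274 |
| 30 % drop-out | −ln 0.7 / 5 = 0.0713 | 0.2100 | 0.65 / 0.2100 = 3.096 |

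**Level.** 3.274 / 3.607 = 0.908, so 20 % drop-out understates mean 5-year cost by 9.2 %. If 20 % is instead the share actually seen to leave before death, e must satisfy e × m = 0.20. That gives e = 0.0636, m = (1 − 0.364) / 0.2022 = 3.146 years and an understatement of 1 − 3.146 / 3.607 = 12.8 %.

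**Comparison, equal survival and equal cost per year.**
- Drop-out 20 % in both arms: both means shrink by the same factor and no false difference arises. A real difference in cost per year would be shrunk by the same 9.2 %.
- Drop-out 10 % v 20 %: 3.274 / 3.444 = 0.951, a false difference of 4.9 %.
- Drop-out 10 % v 30 %: 3.096 / 3.444 = 0.899, a false difference of 10.1 %.

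A simulation with 375 patients per arm and an assumed coefficient of variation of 0.3 for yearly cost gives the chance that a two-sided 5 % t test wrongly declares a given arm cheaper. It is about 2 % with 20 % drop-out in both arms. For the arm with more drop-out, it is about 60 % at 10 % v 30 %.

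**Death, kept separate.** At hazard ratio 1.31 and no drop-out, the hazard is 1.31 × 0.1386 = 0.1816, and the mean is (1 − 0.403) / 0.1816 = 3.286 years. The ratio 3.286 / 3.607 = 0.911 is 8.9 % less cost. Every total here is complete, so this is a true difference in mean cost.

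**The case against.** The strongest objection is that the article never defines the cost variable. If cost is analysed per month or year, truncation at drop-out has a different and perhaps smaller effect, and a condensed article may leave that definition to the full protocol. This stands as a condition on the size of the bias. It does not remove the point, because the article does fix the test, and a t test or ANOVA makes no allowance for incomplete follow-up. A cost rate is not automatically safe either: the Discussion expects dialysis dose to rise as clearance falls, so early leavers would mainly contribute the lower-volume months.

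A second objection also stands in part: the plan gives one overall drop-out rate and the same censoring in each group. The unequal splits above come from no document. They show sensitivity and are not a forecast.

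Third, the analysis sets might absorb the problem. They do not. Carrying a cumulative total forward keeps the truncated total; applied to period costs, it could add cost after death. The per-protocol set removes many drop-outs by selection and still keeps those who left for lack of effectiveness. The 20 % figure cannot, however, be applied directly to that set.

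A reader might go further and infer that the t test turns earlier death into a false saving. The documents do not support that. A patient who dies has a complete cost, and a censoring-adjusted estimator would show the same 8.9 %. The risk there lies in reading the cost result without the survival result. Nor does the policy argument make cost decisive: the Discussion's stated decision turns on non-inferiority, and survival and drop-out are themselves compared between arms.

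**Conclusion.** The point holds in a limited form. On the cumulative reading, the stated method gives means that are too low under the drop-out the plan itself expects: by about 9 %, or about 13 % if the 20 % is read as the share actually observed to leave. It gives a false difference between arms only if drop-out differs: 4.9 % and 10.1 % in the two illustrations. These sizes rest on constant cost per year, exponential times and drop-out spread over the 5 years. The effect of earlier death is real and is a matter of interpretation. Cost is a secondary outcome, and the primary survival conclusion is untouched. The change is worth making because it is cheap and confined to the analysis.

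**What to change.** Define the measure as cumulative medical cost per patient from randomisation to 5 years. Replace the t test or ANOVA with a difference in censoring-weighted mean cost (Bang–Tsiatis type) in all randomised patients, with bootstrap confidence intervals. Treat death as complete and drop-out as censored, and state that cost is not carried forward. Report the result beside 5-year restricted mean survival and cost per patient-month, so that a lower total caused by shorter survival is seen for what it is.

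The price is somewhat wider intervals and a little more programming. The weighting also assumes that drop-out is independent of cost given the recorded covariates, which should be examined in a sensitivity analysis. The partitioned form of the estimator needs dated costs; if these are not recorded, the simple weighted form can be used.
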